### Baseline characteristics

The baseline characteristics are evaluated at approximately 20 weeks of pregnancy. The variables to be measured include age; delivery experience; history and type of allergy of the subject, their partner, and siblings; type of pet, if any; and smoking status of the subject and her family members living together.

### Participant timeline

Table 2 shows the consent forms obtained from the subjects, the intervention, and the evaluation schedule.

**Table 2 Tab2:** Consent, enrolment/allocation, and assessment of subjects (Additional file 2)

	Study period							
	Enrollment Allocation	Post allocation						
Time point	Early pregnancy	20 weeks of pregnancy	30 weeks of pregnancy	Delivery	Discharge	1 month after delivery	4 months after delivery	12 months after delivery
Enrollment/allocation:								
Inclusion	●							
Obtaining informed consent	●							
Randomization	●							
Baseline survey		●						
Interventions:								
Educational program		●	●					
Established childbirth education		●	●					
Assessments:								
Questionnaire survey on living habits, awareness, and knowledge of mothers before and after pregnancy			●			●	●	●
Survey on the behavioral characteristics of mothers						●	●	●
Blood collection from mothers	●		●					
Blood collection from infants (IgE and TARC)							●	●
Stratum corneum hydration of infants					●	●	●	
TEWL of infants					●	●	●	
Findings on the skin of infants (scoring atopic dermatitis (SCORAD)) [50]					●	●	●	
Images of the skin of infants					●	●	●	
Diagnosis of atopic dermatitis in infants							●	●
Diagnosis of food allergy in infants							●	●
Provision of moisturizer					●	●	●	
Collection of the moisturizer container						●	●	●

Legend: *IgE* immunoglobulin E, *SCORAD* scoring atopic dermatitis, *TARC* thymus and activation-regulated chemokine, TEWL transdermal water loss

### Sample size

In this study, the number of deliveries per month at the investigational site was estimated at 15–20, or more than approximately 200 childbirths per year. Moreover, with the current Japanese infant medical checkup system, it is unlikely that the mother will avoid the hospital in the first 4 months after delivery. Therefore, assuming a minimal recruitment rate of 70% and a less than 10% dropout rate, we expect a total of 120 (200 × 0.7 × 0.9 = 126) participants in our study. A questionnaire aimed at identifying the behavioral characteristics of mothers was created for the study to assess primary outcomes. Currently, there are no data showing the effectiveness of the survey sheet. Considering the inclusion of 60 subjects per group with a significance level of 0.05 and a standard deviation of 16 under the conditions described above, the expected upper limit of the standard error of the mean was approximately eight using a *t* test with a statistical power of 80%. Based on this estimate, the final target sample size was set at 120 patients. The statistical power was calculated using R ver.3.5.2 statistical software (R Foundation for Statistical Computing, Vienna, Austria).

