**Methods/design:**

We designed a randomized controlled, two-arm (standard prenatal education vs our education), parallel-group, assessor-blind trial. A sample of 120 pregnant women will be recruited at Chiba Aiyu-kai Kinen Hospital and allocation is by computer-generated randomization.

Pregnant women in the intervention arm participate in the childbirth education program established by the specialist and a pediatric allergy educator. The program was developed based on evidences supporting interventions on primary prevention, which are suggested to be beneficial to infantile allergies in recent studies.

The primary objective of the study is to determine whether it is possible to establish effective behaviors for allergy prevention in early infancy in the children of pregnant women who participate in an educational program developed by pediatric allergy specialists. Four months after birth, their behaviors will be compared against those of pregnant women who did not participate in the program.

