### Primary outcomes

#### Self-evaluation of questionnaire to identify the behavioral characteristics of mothers based on the educational program at 4 months after delivery

A linear mixed-effects model is used to analyze the total score of the questionnaire at 1, 4, and 12 months after delivery as an outcome variable. A mixed-effects model for repeated measurements (MMRM) [51] is used to properly handle missing values or dropouts that could arise during the study. An unstructured covariance structure is used to assess the correlation between outcomes at these time points. Mean changes from baseline are modeled as outcome variables for the MMRM. Mean changes from baseline at each time point are analyzed individually using a regression model. If the regression parameters cannot be estimated using the unstructured model, the covariance structure is changed in the following sequence: Toeplitz matrix model, heterogeneous compound symmetry model, autoregressive model (1), compound symmetry model, and variance components model. A primary analysis is performed using estimates for the regression parameter or regression parameter test at 4 months after delivery. The significance level is set at 5% (two-sided).

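### The sample-size statement labels the detectable difference of about eight points a standard error of the mean, and the protocol does not settle whether 120 is the number recruited or the number left after dropout

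*Protocol article*

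**What the plan says.** The Sample size section of the protocol article does two things.

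- **Accrual forecast.** It starts from about 200 births a year, "assuming a minimal recruitment rate of 70% and a less than 10% dropout rate", multiplies 200 × 0.7 × 0.9 = 126, and expects 120 participants.
- **Power statement.** It then reads "Considering the inclusion of 60 subjects per group with a significance level of 0.05 and a standard deviation of 16", adds a t test with 80% power, and reports that "the expected upper limit of the standard error of the mean was approximately eight". On that basis it fixes the target at 120. No difference between the arms is named as the one to be detected, and no source is given for the SD. The section also says that no data yet exist on how the survey sheet performs.

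The section does not say whether the 5% level is one- or two-sided. The analysis section for the primary outcome makes it two-sided.

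The Abstract (Methods/design) says: "A sample of 120 pregnant women will be recruited".

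**The concern.** A standard error of a mean depends only on the SD and the number of subjects. It does not depend on alpha or power, so a calculation that uses both cannot have produced one. The figure also has the wrong size: eight is half of the assumed SD, which is the standard error for a group of four, not sixty.

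This sentence is the protocol's only justification for the size of a superiority trial. Taken literally, it says that a group mean is known about four times less precisely than it will be (8 / 2.07 = 3.9). It also leaves the trial without a correctly stated difference for which 80% power is claimed.

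The second problem is what 120 counts. The power calculation needs 60 analysed per group. The forecast treats 120 as what is left after dropout, but the Abstract treats it as the intake. If enrolment stops at 120, no margin remains for the dropout that the protocol itself expects.

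**Working it through.** **Inputs.** SD 16, 60 per group, alpha 0.05, 80% power, t test, dropout below 10%, 200 births and 70% recruitment (all Sample size section); two-sided testing (primary outcome analysis); 1:1 allocation (Randomization section); 120 recruited (Abstract).

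**Step 1. Is eight a standard error?**
- Standard error of one group mean: SD/√n = 16/√60 = 2.07.
- Standard error of the difference: SD × √(2/n) = 16 × √(2/60) = 2.92.
- For a standard error of the mean to equal 8 with SD 16, n = (16/8)² = 4. With n = 60, the SD would have to be 8 × √60 ≈ 62.

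Neither standard error is near eight.

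**Step 2. What does reproduce eight?** The minimum detectable difference for a two-sample comparison:
- Normal approximation: (1.960 + 0.842) × 16 × √(2/60) = 2.802 × 2.921 = 8.18.
- Noncentral t, two-sided 5%, 80% power, 60 per group: 8.25.
- The same with a one-sided test: 7.31.

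The two-sided value rounds to about eight, so the plan's figure is reproduced as a detectable mean difference. In SD units it is 8.25/16 = 0.52.

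**Step 3. The two meanings of 120.**

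| Reading | Randomised | Analysed per group | Detectable difference at 80% (t) | Power for 8.25 |
|---|---|---|---|---|
| 120 evaluable | 120/0.9 = 133.3, so 134 | 60 | 8.25 | 80% |
| 120 randomised, 10% lost | 120 | 120 × 0.9 = 108, so 54 | 8.71 | about 76% |

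For the second row, the standard error of the difference is 16 × √(2/54) = 3.08. The noncentrality at 8.25 is 8.25/3.08 = 2.68, and the noncentral t gives a power of about 0.757. The normal approximation to the detectable difference is 2.802 × 3.079 = 8.63.

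**Step 4. Can the forecast support the first reading?** 200 × 0.7 = 140 women consenting, against 134 needed. With 140 × 0.9 = 126 completing (63 per group), the detectable difference is 8.05. The plan's own forecast is therefore sufficient if enrolment is not stopped at 120.

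**The case against.** A reader might infer that the plan ignores dropout and so does not deliver its stated 80% power. The text does not support that. The Sample size section multiplies by 0.9 and still arrives at 126, above 120. Read in order, 120 is a number after dropout, and the 60 per group in the power sentence are the women who remain. On that reading 80% power for 8.25 points is delivered. The contrary reading rests mainly on the Abstract sentence, since a target of 120 in the Sample size section fits either meaning. This objection stands: the shortfall is conditional.

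The conditional loss is also modest. Ten percent is the document's upper limit, and the section argues that mothers are unlikely to miss visits in the first four months. The calculation gives no credit to women who drop out after a 1-month score, whereas the repeated-measures model planned for the primary outcome would use those scores. The shift in detectable difference is 8.71 − 8.25 = 0.46 points.

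A reader might also infer that a null result could not be interpreted. That goes too far. The group size, SD, alpha, test and power are all given, so 8.25 can be recovered. What a null result excludes will depend on the observed confidence interval.

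None of this touches the label. Condensing a protocol into an article does not turn a detectable difference into a standard error.

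**Conclusion.** The label is an error, certain on the document's own inputs: the standard error of the mean is 2.07, the standard error of the difference is 2.92, and about eight is the two-sided detectable difference of 8.25 points. It needs correcting because this sentence alone justifies the trial's size.

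The meaning of 120 is an unresolved conflict between the Abstract and the Sample size section, not a demonstrated loss of power. If 120 is evaluable, nothing is lost. If 120 is randomised, power for 8.25 falls at worst to about 76% and the detectable difference rises to about 8.7.

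These figures take SD 16 as given, equal groups, a two-sided 5% t test, and for the adverse case the full 10% dropout with no information recovered from earlier scores.

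**What to change.** 1. Replace the standard-error phrase with: *With SD 16, two-sided alpha 0.05 and 60 analysed per group, the trial has 80% power to detect a mean difference of about 8.25 points.*
2. State in both the Abstract and the Sample size section whether 120 is evaluable or randomised.
   - If evaluable, say that about 134 women will be randomised (120/0.9), within the forecast of 140 consenting.
   - If randomised, say that at the 10% dropout limit (54 per group) power for 8.25 points is at worst about 76% and the detectable difference about 8.7, before any information the mixed model recovers from women with earlier scores.

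The cost is wording. On the second reading the stated power becomes slightly less favourable. On the first, the 14 women beyond 120 already lie within the plan's recruitment forecast.

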### Randomization procedure and concealment of allocation

Participants who meet the eligibility criteria and agree to participate in the study are randomized after signing the informed consent form. These subjects are stratified according to the estimated delivery date into winter and other seasons, and randomized using the permuted-block method. A statistical analyst generates a random allocation code using R statistical software (R Foundation for Statistical Computing) to randomize the subjects at each investigational site. The study is an assessor-blinded trial, and all raters are blinded with respect to the assignments. Also only the statistical analyst is aware of the stratification block size; the remaining staff is blinded. Subjects are randomized in a 1:1 ratio into one of two groups.

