### Secondary outcomes

#### Incidence and severity of atopic dermatitis and eczema infantile

The incidence of infantile AD and eczema infantile is compared between groups at all time points using Pearson’s chi-squared test. The severity of these diseases is compared between groups using descriptive statistics of scores at each time point. Subgroup analyses are performed to assess the incidence and severity of AD related to the amount and frequency of moisturizer used during the study and the skin condition of infants.

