#### Frequency of use and amount of moisturizer

Descriptive statistics of the total amount of moisturizer and rate of changes in the scores at each time point are calculated and compared between groups. An evaluation is performed considering birth month as a baseline characteristic.

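### Randomisation is stratified by delivery season, but the stated tests for the binary infant outcomes ignore the stratum and the printed primary model does not mention it; the cost is a modest loss of precision

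*Protocol article*

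**What the plan says.** **Randomisation.** In the section on randomisation and concealment: "These subjects are stratified according to the estimated delivery date into winter and other seasons, and randomized using the permuted-block method". The ratio is equal: "Subjects are randomized in a 1:1 ratio into one of two groups". Delivery season is the only stratification factor named.

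**Binary infant outcomes.** In the analysis section on AD and eczema: "The incidence of infantile AD and eczema infantile is compared between groups at all time points", by Pearson's chi-squared test. The analysis section on food allergy and sensitisation names the same test. Neither mentions the stratum.

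**Primary outcome.** The analysis section gives the response variable, the visits, an unstructured covariance with a fallback sequence, the 4-month decision point and a two-sided 5% level. It lists no fixed effects, so season is neither included nor excluded.

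**Where a seasonal variable is used.** Only under frequency and amount of moisturiser: "An evaluation is performed considering birth month as a baseline characteristic".

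**Baseline data.** Age, parity, family allergy history, pets and "smoking status of the subject and her family members living together" are recorded at about 20 weeks. Table 2 places this after randomisation and in the same column as the first educational session.

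**The concern.** Balancing the arms on a factor removes its chance imbalance from the treatment comparison. An analysis that ignores the factor still counts its variation as noise. The reported standard error is then larger than the true one, and the benefit of stratifying is partly thrown away.

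The sponsor chose season as its sole stratifier, presumably expecting it to matter for infant skin or for mothers' behaviour. The article nevertheless brings a seasonal variable into the analysis of one secondary outcome only. At stake is some precision on the binary infant outcomes and, if season is also absent from the full model, on the primary score.

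**Working it through.** **Inputs from the Sample size section:** "Considering the inclusion of 60 subjects per group with a significance level of 0.05 and a standard deviation of 16"; power 80%; and "the final target sample size was set at 120 patients". The two-sided 5% level comes from the primary analysis section. The documents give no season effect, winter share or event rates, so those below are assumptions.

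**Step 1: the plan's own figure.** The article says "the expected upper limit of the standard error of the mean was approximately eight using a" t test. As a detectable mean difference:
- Normal approximation: (1.960 + 0.842) × 16 × √(2/60) = 2.802 × 2.921 = 8.18.
- Exact t: 8.25.

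Both fit the stated value of about eight. A standard error would be 2.07 per arm (16/√60) or 2.92 for the difference, so the figure is read here as a difference.

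**Step 2: what season could explain.** With an assumed 25% winter share, R² = 0.25 × 0.75 × D² / 16², where D is the winter-versus-other gap in the score.

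| D (points) | R² |
|---|---|
| 4 | 3/256 = 0.012 |
| 8 | 12/256 = 0.047 |
| 12 | 27/256 = 0.105 |

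**Step 3: primary score, stratum ignored or included.** Normal approximation, 60 per arm, difference 8, standard error 2.921 before adjustment.
- Type I error, stratum ignored: 2 × [1 − Φ(1.96/√(1 − R²))].
- Power, stratum ignored: Φ[(8/2.921 − 1.96)/√(1 − R²)].
- Power, stratum included: Φ[8/(2.921 × √(1 − R²)) − 1.96].

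| Season R² (assumed) | Type I error, ignored | Power, ignored | Power, included | Gain (points) |
|---|---|---|---|---|
| 0 | 5.0% | 78.2% | 78.2% | 0 |
| 0.02 | 4.8% | 78.4% | 79.0% | 0.6 |
| 0.05 | 4.4% | 78.8% | 80.2% | 1.4 |
| 0.10 | 3.9% | 79.4% | 82.3% | 2.9 |

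The comparator is the unadjusted analysis at the same R². Stratified randomisation has already made that estimate more precise, so setting adjusted power against the R² = 0 row would overstate the gain.

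**Step 4: binary outcomes.** 20,000 simulated trials per setting, with 15 winter and 45 other births per arm and an odds ratio of 0.35 (all assumed). Pearson's test is compared with the Cochran-Mantel-Haenszel (CMH) test stratified by season.

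| Control rate, winter / other | Type I error, Pearson / CMH | Power, Pearson / CMH |
|---|---|---|
| 30% / 30% | 5.0% / 4.6% | 63.2% / 62.3% |
| 45% / 25% | 5.0% / 5.2% | 61.9% / 62.6% |
| 60% / 20% | 3.7% / 5.2% | 53.8% / 58.5% |

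The simulation standard error of each power figure is about √(0.6 × 0.4/20,000) = 0.35 points. The middle row is therefore close to a tie. A clear gain, 58.5 − 53.8 = 4.7 points, appears only with the strong assumed season effect.

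**The case against.** **The primary model may already contain season.** A reader might infer that the primary analysis is unadjusted. The article does not say so. It lists no fixed effects at all, not even treatment, and a condensed article commonly leaves that list to the full protocol or analysis plan. This objection stands. For the primary model the point is conditional.

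**Larger gains are not supported.** A reader might also expect season together with age, parity, family history and smoking to explain 10 to 20% of the score variance, which would cut the detectable difference from 8.25 to between 7.83 and 7.38. Nothing in the article shows how strongly these variables predict the score. Smoking has the clearest link, since two of the 21 items concern it. But it is recorded after allocation and alongside a session that teaches about smoking.

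**Season may predict the score only weakly.** The stratum is season of delivery, while the primary score describes behaviour four months later. Winter births answer in about spring or early summer, and autumn births, in the other stratum, answer in about winter. For the sunlight and outdoor items the stratum is therefore a poor marker of season at response. In Step 2, an R² near 0.05 needs a gap of about 8 points, as large as the planned treatment difference. This also stands, and it is why the range starts at zero.

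**Pearson's test is valid and the outcomes are secondary.** True. But the unstratified test is stated outright, so silence in a condensed article does not explain it, and the stratified alternative costs almost nothing.

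**Conclusion.** The point holds in a limited form. The mismatch between stratified randomisation and the unstratified chi-squared tests is explicit. For the primary model the article shows only that season is not mentioned.

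The consequence is lost precision. It would be wrong to conclude that the tests are invalid or too liberal, because ignoring a prognostic stratum holds type I error at or below 5%. The gain from correcting it is about 0 to 3 power points on the score for a season R² up to 0.10. For the binary outcomes it runs from about −1 to +5 points. These sizes rest on assumed season effects, a 25% winter share and assumed event rates.

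Nor does this point show that the trial is underpowered. The exact detectable difference of 8.25 agrees with the article's approximate eight, and the article does not fix exactly 8 as its target. This is a worthwhile, low-cost refinement.

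**What to change.** 1. Replace Pearson's chi-squared test for AD and eczema, food allergy and sensitisation with a Mantel-Haenszel comparison stratified by season, reported as a risk difference with confidence interval. Use the stratum as randomised, that is, by estimated delivery date.
2. State whether the season stratum is a fixed effect in the primary mixed model, and add it if the full protocol or analysis plan does not already include it.
3. Adjustment for age, parity and family allergy history is optional, and its benefit cannot be quantified from the article. If wanted, name the covariates in advance.
4. Use smoking status as a covariate only if it is recorded before the first session. That means moving a short form to the enrolment visit. For women already enrolled it may have to be left out.

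Items 1 and 2 need only wording, because the stratum is known for every randomised woman.

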### Statistical analysis

#### Full analysis set

Subjects enrolled in the study who started any of the study procedures are included in the full analysis set (FAS). However, those with a confirmed serious deviation from the protocol and those determined ineligible for the study after enrollment are excluded from the FAS.

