### Trial design

This study is an assessor-blinded, randomized controlled, parallel-group comparison study (comparing our educational program group with an established childbirth education group) conducted in Chiba Aiyu-kai Kinen Hospital (hereafter referred to as “our hospital”) to examine the superiority of the educational program over established programs. Subjects are randomized in a 1:1 ratio into one of the two groups. The participants and study personnel are not blinded with respect to the assignments.

This protocol is written in accordance with the Standard Protocol Item: Recommendations for Interventional Trials (SPIRIT) guideline. Trial registration is through the University Hospital Medical Information Network – Clinical Trials Registry (UMIN-CTR) (UMIN000034730).

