### Participants

#### Recruitment procedure

Participants are recruited among all pregnant women who visit our hospital for consultation regarding delivery. The investigator meets with each pregnant woman to provide oral and written information on the study and to request participation. Participants are selected according to the eligibility criteria. The pregnant women discuss participation with their respective families, and those who agree to participate in the study provide informed consent. After the collection of consent forms, the participants are randomized to one of two groups.

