#### Intention-to-treat analysis

In general, all statistical analyses are performed by the intention-to-treat principle.

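### The full analysis set removes randomised women for serious deviations and for ineligibility found later, which conflicts with the intention-to-treat statement

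*Protocol article*

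**What the plan says.** The Full analysis set section of the protocol article starts from enrolled women who began any study procedure. It then states that "those with a confirmed serious deviation from the protocol and those determined ineligible for the study after enrollment are excluded from the FAS". The next section, Intention-to-treat analysis, reads: "In general, all statistical analyses are performed by the intention-to-treat principle". No second analysis set appears anywhere in the article.

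On timing, the Recruitment procedure section says: "After the collection of consent forms, the participants are randomized to one of two groups". Table 2 (Participant timeline) places the row "Randomization" in early pregnancy, before the baseline survey at 20 weeks and well before delivery. The exclusion criteria under Eligibility criteria include abnormal birth, serious congenital malformation of the child, and women or neonates whom a physician considers unsuitable.

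On blinding, the Trial design section says: "The participants and study personnel are not blinded with respect to the assignments". The Randomization procedure section adds that raters are blinded. Neither section covers the decision to exclude a woman from analysis.

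**The concern.** Randomisation protects the comparison only for the groups as they were randomised. A rule that removes women for what happened after allocation can leave two groups that differ for reasons other than the programme. The trial aims "to examine the superiority of the educational program over established programs", and in a superiority comparison such removals are not conservative by default: if the women removed from one arm tend to be low scorers, the apparent effect grows.

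The exclusions are also unnecessary for the primary outcome, which is the mother's own behaviour score four months after delivery. A mother who had an abnormal birth can still answer the questionnaire. The article chooses a mixed model for repeated measures in order to handle missing data and dropout properly, and deleting randomised women before the model is fitted gives up part of that protection.

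**Working it through.** **1. The two rules side by side.**
- Intention to treat: every randomised woman is analysed in her allocated arm, whatever her adherence.
- FAS as written: a randomised woman leaves the set if she has a confirmed serious deviation or is later found ineligible. Requiring that a study procedure was started is a further, smaller restriction.
- The opening words of the intention-to-treat sentence soften it, but they name no exception and do not refer to the FAS exclusions. Both statements cannot govern the same primary analysis.

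**2. When the criteria become known.**
- Randomisation: early pregnancy (Table 2).
- Abnormal birth: only at delivery.
- Neonate judged unsuitable: only after delivery.
- Serious malformation: largely at or near birth, although some cases may be detected earlier.

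The FAS section does not list birth events. That they lead to removal is an inference, but a direct one: they are exclusion criteria, and women found ineligible after enrolment are removed.

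**3. The plan's own figures, for scale.** The Sample size section gives 60 women per arm, a standard deviation of 16, 5% significance, 80% power and a value of about eight.
- Recruitment: 200 × 0.7 × 0.9 = 126, as stated.
- The article words the eight as a standard error. The standard error of the difference is 16 × √(2/60) = 2.92, so eight fits only as a detectable difference. A t test with 60 per arm and 80% power detects 8.25.
- Power for a difference of exactly 8 is 78.2% (normal approximation) or 77.5% (t test).

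The point made here does not depend on these figures.

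**4. Illustration of possible bias.** The documents give no exclusion rates, so every input except the standard deviation, the arm size and the 5% level is assumed. Let a share f of one arm be excluded, none of the other, and let the excluded women score k points below the rest of their arm. Then:
- full arm mean = retained mean − f × k, so the shift is f × k;
- SE = 16 × √(1/60 + 1/(60(1 − f)));
- two-sided type I error = 1 − Φ(1.96 − shift/SE) + Φ(−1.96 − shift/SE).

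For f = 0.10, 54 women remain and SE = 16 × √(1/60 + 1/54) = 3.00. With k = 8, shift/SE = 0.8/3.00 = 0.27. With k = 16, it is 1.6/3.00 = 0.53.

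| Excluded from one arm | Shift, k = 8 | Type I error | Shift, k = 16 | Type I error |
|---|---|---|---|---|
| 5% | 0.4 | 5.2% | 0.8 | 5.8% |
| 10% | 0.8 | 5.8% | 1.6 | 8.3% |
| 15% | 1.2 | 6.8% | 2.4 | 12.4% |

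At 10% the shift is 0.8/8 = 10% to 1.6/8 = 20% of the eight-point difference.

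**5. If exclusions were unrelated to arm and score.** Losing 10% of both arms would lower power for a difference of 8 from 78.2% to 73.8% (normal approximation), with no bias.

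**The case against.** The strongest reply is that the conflict is one of wording and that harm is not demonstrated. A condensed article may leave the definition of a serious deviation to the full protocol, and birth events are unlikely to depend much on an educational programme. Both points are fair, and they limit the claim to possible bias. They do not reconcile two adjacent statements that contradict each other.

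A reader might infer three stronger things that the documents do not support.

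- **That only intervention mothers can be removed for missed sessions.** The Control arm section mentions only a leaflet. However, Trial design calls the comparator an established childbirth education group, Table 2 schedules that education at 20 and 30 weeks, and eligibility requires every woman to plan to attend the hospital's programme. The section on safety and compensation gives about 180 minutes of sessions without limiting this to one arm. Control women may therefore also have sessions to miss, and nothing says that non-attendance counts as a serious deviation.
- **That unblinded staff decide the exclusions.** The article says that personnel know the allocation. It does not say who confirms a deviation or ineligibility, or whether this is done blind. The defect is that no blinded decision is stated.
- **That type I error could approach 18%.** The arithmetic gives 17.8%, but only if 20% of one arm and none of the other are excluded with a full 16-point gap. The only attrition figure in the article is a dropout rate below 10%.

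**Conclusion.** The conflict holds as written. The only defined analysis set applies a per-protocol rule while the stated general principle is intention to treat. Because some criteria cannot be assessed until around delivery, following the plan will exclude women after randomisation whenever such events occur.

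The size of any bias is unknown. Its direction depends on what is counted as a serious deviation, on how often that happens in each arm, and on how the removed women would have scored. The 0.8 to 1.6 points and the 6 to 8% type I error at 10% one-sided exclusion illustrate what the rule could allow; they do not predict what it will do. Removals for birth events threaten the randomised comparison in principle, and precision in practice, more than they suggest a large bias. The matter should be settled before analysis because the rule decides who enters the primary comparison.

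**What to change.** For the primary maternal questionnaire outcome, define the primary analysis set as all randomised women, analysed in their allocated arm, with every available post-delivery score entering the repeated-measures model. Report women with no score by arm and reason. Withdrawals belong in that count and should not be assumed unrelated to arm.

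Move exclusions for serious deviation and for ineligibility found later to a per-protocol sensitivity analysis. Define a serious deviation in advance, and have each exclusion decided blind to arm before database lock. The eligibility criteria themselves need not be rewritten for this purpose.

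The cost is mainly wording, submitted as a protocol amendment; the target of 120 does not change. It is not entirely free: women with an abnormal birth or with ineligibility found later must stay in questionnaire follow-up, which the article does not now promise, and keeping non-adherent women may slightly dilute the estimated effect.
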